1.2.3.5 Dose recommendation

Taking into consideration the average weight of the Chinese population, receptor occupancy, probability of immunogenicity, clinical convenience, dosages of similar drugs, efficacy, and safety, a proposed fixed dose of 1200 mg per administration every 3 weeks is recommended for later-stage trials. This dosage will be further validated for safety and efficacy in subsequent trials.

1. Study objective

ALTER-L038 study aims to evaluate the efficacy and safety of the combination including anlotinib and TQB2450 in EGFR-positive advanced NSCLC patients who failed prior EGFR-TKIs therapies.

1. Study design
   1. Overall design

This is a multicenter, open-label, single-arm, phase I/II study aimed at evaluating the efficacy and safety of the combination including anlotinib and TQB2450 in EGFR-positive advanced NSCLC patients who failed prior EGFR-TKIs therapies.

The first stage of the study is a phase I 3+3 dose-escalation study, starting with 8 mg anlotinib in combination with 1200 mg TQB2450 as the initial dose, with three dose levels set at 8 mg/10 mg/12 mg. Phase I study is expected to enroll 18 participants.

The second stage is a multicenter, single-arm phase II study using the MTD determined in the first stage, with an estimated enrollment of 54 participants. This study started in August 2019, with recruitment concluding around August 2020, and the estimated end date is August 2021.

In the absence of withdrawal of consent, intolerable side effects, or a decision by the investigator to be inappropriate for further trial, treatment is continued for each subject until radiographically confirmed disease progression.

- 1. Type of comparison

The phase I study is designed for descriptive statistics without comparative analysis.

The phase II study is a single-arm study using historical controls. The primary efficacy endpoint is PFS. A statistically significant extension in PFS compared to historical controls, reaching a clinically meaningful difference (defined as a PFS extension of ≥4 months when comparing the trial and historical groups, using 30.5 calendar days as a month), would be considered a positive outcome for the study.

- 1. Sample size calculation

Phase I part: Following the 3+3 dose-escalation design, the study anticipates a minimum of 3 and a maximum of 18 participants to be enrolled.

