Phase II part: Based on prior efficacy data achieved with carboplatin plus pemetrexed in EGFR+ NSCLC patients who failed to EGFR-TKI, an mPFS of 5 months was utilized as a historical control to determine the sample size for the phase II part. We hypothesized that TQB2450 plus anlotinib would lead to clinical benefit in this population, with a mPFS of 9 months. Sample sizes of 54 in the study achieved 90% power at a significance level (α) of 0.05 with an anticipated dropout rate of 20%. The study is expected to last for 24 months, including a 12-month patient enrollment period. At the study's conclusion, an estimated 32 endpoint events are expected to occur.

1. Subjects
   1. Diagnostic criteria

Diagnostic criteria: the diagnosis will be confirmed according to the sixth edition of Oncology Diagnostics and the sixth edition of Internal Medicine published by the People's Medical Publishing House of the People's Republic of China.

- 1. Inclusion criteria

The inclusion criteria were:

1. Male or female, aged 18-75 years;
2. Histologically and cytologically confirmed locally advanced/advanced NSCLC, assessed as stage IIIB-Ⅳ NSCLC (according to the 8th edition of the tumor–node–metastasis staging system of the American Joint Committee on Cancer), or NSCLC patients with postoperative recurrence (all types);
3. Patients with EGFR-positive (EGFR+) NSCLC with failure of prior EGFR-TKIs, or *T790M* mutation with failure of prior 3^rd^-generation EGFR-TKIs;
4. EGFR-TKIs should be the mainstay of the initial treatment for patients. Patients are allowed to receive ≤1 systemic chemotherapy;
5. Patients with previous only 1^st^/2^nd^-generation EGFR-TKIs were required to provide genetic testing reports showing no primary or acquired T790M mutation; patients with previous 3^rd^-generation EGFR TKIs were required to provide genetic testing reports showing EGFR mutation was positive;

Treatment failure is defined as (1) the PD assessed by imaging or clinical evidence during or after EGFR TKIs treatment, or withdrawal from standard treatment for intolerant AEs. The intolerant AEs included grade Ⅳ hematologic toxicity, or grade ≥Ⅲ nonhematologic toxicity, or grade ≥Ⅱ main organ damage such as heart, liver, and kidneys per Common Terminology Criteria for Adverse Events (CTCAE) version 5.0.

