**8.2.1 Sample size**

Phase I: Following the 3+3 principle of dose adjustment, a minimum of 3 and a maximum of 18 patients were expected to be enrolled.

Phase Ⅱ: The mPFS of TQB2450 plus anlotinib hydrochloride capsules was estimated to be 9 months, and the historical control group carboplatin combined with pemetrexed was set as 5 months. The two-sided test level α was 0.05, and the power level was 0.90. It was calculated that 54 subjects would need to be enrolled (considering that the loss to follow-up rate should be controlled at 20%). The study was expected to last 24 months, including 12 months after enrollment. At the end of the study, 32 end-point events were expected to have occurred.

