ORR is defined as the percentage of subjects with confirmed tumor volume reduction to pre-specified values and lasting for ≥4 weeks, including subjects with a PR or CR. Objective responses are assessed per RECIST v1.1. Subjects must have at least one measurable lesion at baseline. The response was classified as CR, PR, SD, and PD according to RECIST v1.1.

For PFS, OS, and DOR, Kaplan-Meier was used to estimate median survival and draw survival curves, and the 1-year disease progression rate and 1-year survival rate were also estimated. For ORR and DCR, the Clopper-pearson method was used to estimate 95% confidence intervals.

1. **Project management**
   1. **Information promulgation**

The present study will be registered and publicized in the Chinese Clinical Trial Registry after obtaining ethical approval from the responsible unit of the clinical study.

- 1. **GCP and ethics committee review and approval**

This clinical trial will be conducted in accordance with the Declaration of Helsinki (2013), the GCP promulgated by the NMPA and related regulations. The investigator will not begin any study subject activities until approval from the Clinical Research Ethics Committee of the Clinical Trial Team leader. Any modifications of the protocol during the clinical study should be declared and filed to the Ethics Committee.

Clinical investigators will follow all applicable regulations to protect subjects. The informed consent document used in the trials must be reviewed by the sponsor, approved by the ethics committee, and available for inspection.

- 1. **Informed consent**

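### The trial counts as positive only if the observed PFS gain reaches the full 4 months assumed in the design, so at a true median of 9 months the chance of success is about 50%, not the stated 90%

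*Protocol*

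**What the plan says.** Section 3.2 (Type of comparison) names PFS as the primary efficacy endpoint and defines success for the single-arm phase II part in one sentence. It requires "A statistically significant extension in PFS compared to historical controls, reaching a clinically meaningful difference", the latter "defined as a PFS extension of ≥4 months when comparing the trial and historical groups", and says that this "would be considered a positive outcome for the study". The same sentence fixes a month at 30.5 days.

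Section 3.3 gives the control value: "an mPFS of 5 months was utilized as a historical control to determine the sample size for the phase II part". Section 8.2.1 gives the alternative: "The mPFS of TQB2450 plus anlotinib hydrochloride capsules was estimated to be 9 months". On power, Section 3.3 says "Sample sizes of 54 in the study achieved 90% power at a significance level (α) of 0.05" and Section 8.2.1 says "The two-sided test level α was 0.05, and the power level was 0.90". Both allow for 20% dropout, a study of 24 months and 32 expected events; Section 3.3 puts enrolment at 12 months.

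The synopsis repeats the sample size paragraph but not the 4-month rule. Nowhere does the protocol give the probability of meeting the two-part rule, or relate the 4-month bar to the 9-month assumption.

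**The concern.** The success bar on the observed result (5 + 4 = 9 months) is the same number as the median the trial was designed to detect. An estimate of a median falls above its own true value only about half the time. A rule that requires this cannot have 90% power at that true value, whatever the sample size.

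If the combination works exactly as hypothesised, the trial would therefore miss its own definition of success about one time in two, while investigators and ethics committees read 90%. A result with an observed median between about 7.1 and 8.9 months would be clearly significant and yet not positive. That invites a reinterpretation of the rule once the data are known.

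**Working it through.** **Inputs.** Control median 5 months and alternative 9 months (Sections 3.3 and 8.2.1); two-sided α 0.05 and power 0.90 (8.2.1); 54 patients, 20% dropout, 12 months' enrolment within 24 months, 32 events (3.3); success needs a gain of at least 4 months (3.2). Assumed here: exponential PFS, uniform accrual, control fixed at 5 months.

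**1. The plan's own figures reproduce.**
- Events needed: (1.960 + 1.282)² / [ln(9/5)]² = 30.4.
- Event probability at a median of 9 months, with λ = ln 2 / 9: 1 − [exp(−12λ) − exp(−24λ)] / (12λ) = 0.741.
- Expected events: 54 × 0.8 × 0.741 = 32.0, as stated.
- Patients: 30.4 / 0.741 / 0.8 = 51.3, so 52. A one-sample log-rank calculation gives 42.3 / 0.8 = 52.9, so 53. The plan states 54.
- Power with 32 events: Φ(√32 × ln(9/5) − 1.960) = Φ(1.365) = 0.91.

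The 90% is thus the power to reject a 5-month median. The 4-month requirement plays no part in it.

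**2. Which condition binds?** The smallest significant observed median with 32 events is 5 × exp(1.960/√32) = 7.07 months, a gain of about 2.1 months. Any result that clears 9 months has in practice already cleared significance.

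**3. Probability of the full rule, analytically.** With d events and true median m, P(observed median ≥ 9) ≈ Φ(√d × ln(m/9)).
- At m = 9 this is Φ(0) = 0.50 for every d, so adding patients does not help.
- For 90% with 32 events, m = 9 × exp(1.282/√32) = 11.3 months.

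**4. By simulation** (6,000 trials per scenario; one-sample log-rank significance and Kaplan-Meier median ≥ 9 months):

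| True median | Patients | Significant | Full rule |
|---|---|---|---|
| 9 months | 43, no dropout | 93% | 51% |
| 9 months | 54, 20% dropout | 96% | 51% |
| 9 months | 54, no dropout | 97% | 46% |
| 12 months | 43, no dropout | almost 100% | 90% |
| 12 months | 54, 20% dropout | 100% | 92% |

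Using the exponential estimate of the median instead of Kaplan-Meier gives about 50% in all three 9-month scenarios. At a true 8 months the full rule succeeds in 28–31% of simulated trials.

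**5. Another control figure.** If the gain were measured against the chemotherapy medians in the protocol's background section (4.4 or 5.4 months), the bar would be 8.4 or 9.4 months. The chance at a true 9 months would be Φ(√32 × ln(9/8.4)) = 65% or Φ(√32 × ln(9/9.4)) = 40%.

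**The case against.** **The rule may be read more loosely.** Taken literally, Section 3.2 says what would count as positive, not that anything less is negative; and the 4 months could simply name the design difference, 9 − 5. But the sentence compares the trial group with the historical group and fixes a day-to-month conversion, which only observed data need. It is the only success definition in the protocol. The plain reading is a decision rule on the observed gain.

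**No stated figure is miscalculated.** This is true. Sections 3.3 and 8.2.1 tie the 90% to the test level, and requiring significance plus a minimum observed effect is a legitimate design. The fault is that the quoted power does not belong to the quoted success rule.

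**About 50% assumes progression is seen when it happens.** In the trial it is seen at scans, at the end of odd-numbered cycles with a ±7-day window. If the true underlying median is 9 months and detection waits for the next scan, simulations with 43 patients put the chance of an observed median of at least 9 months at 53% with no window noise and 63% with ±7 days. If enrolment precedes the first dose by an assumed 3 days, the figures become 77% and 68%. If the 9 months is already a scan-measured median, about 50% returns. This qualifies the figure but does not bring it to 90%. The sensitivity arises because the bar, 9 × 30.5 = 274.5 days, lies just beyond the cycle 13 scan at 13 × 21 = 273 days.

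**The test may be specified in the SAP.** The efficacy section says only that "For PFS, OS, and DOR, Kaplan-Meier was used to estimate median survival and draw survival curves", and the synopsis adds 95% confidence intervals. Reading such an interval against 5 months would also give less than 90% (62–77%, depending on how the interval is built). Since the choice of test may properly sit in a SAP that is not at hand, the finding does not rest on this.

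**Conclusion.** The point holds. The sample size is sound for a significance test of 5 against 9 months, but the 90% does not describe the probability of the positive outcome defined in Section 3.2. At a true median of 9 months that probability is about 50%, assuming exponential PFS, uniform 12-month accrual, a fixed 5-month control and the 4 months read as the observed gain. Scan-detection delay could raise it to between 53% and 77%. About 90% is reached only at a true median of roughly 11.3 to 12 months. Because success rule and power statement are both in the protocol and conflict there, the protocol itself needs the correction.

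**What to change.** Choose one of two courses.

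- **(a) Significance alone defines success.** Amend Section 3.2 so that a positive outcome means significantly longer PFS than the 5-month control, and report the observed gain with its confidence interval as a description of clinical relevance. Name a test that the sample size supports, for example a one-sample log-rank test against an exponential distribution with median 5 months. The stated 90% then stands, and the synopsis needs no change to the rule because it does not contain it.
- **(b) Keep the 4-month requirement.** State in the synopsis and Sections 3.3 and 8.2.1 that 90% is the power of the significance test. Add that the probability of a positive outcome at a true 9 months is about 50%, reaching 90% only near 12 months, and give the assumptions on PFS distribution and scan timing.

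Either course changes wording only and adds no patients. Course (b) makes a published figure less favourable.

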| Dropout/Removal Criteria | - 1. Participants who do not meet the screening criteria;   2. Participants who are unable to evaluate for efficacy or unable to evaluate safety without receiving 1 dose of the drug;   3. Participants who are treated with chemotherapy, surgical or experimental drugs other than this protocol during the trial;   4. Participant's concurrent use of China Food and Drug Administration (CFDA)-approved modern herbal agents and immunomodulatory agents for the treatment of tumors;   5. Participants who do not follow the dose, method, and course of treatment according to the study protocol. |
| Termination Criteria | Subject must termination the study if the following cases occur (including but certainly not limited to):   - 1. Disease progression (PD) determined according to RECIST 1.1 criteria or considered clinically progressive.   2. Termination of treatment decided by the investigator from the patient's best interests.   3. Occurrence of intolerable adverse reactions or severe adverse events confirmed by the investigator.   4. Patients with poor compliance, using drug amounts outside the range of 80% to 120% of the prescribed dose.   5. Patient withdrawal of informed consent.   6. Initiation of other anti-tumor drug treatments affecting efficacy judgment (such as chemotherapy, targeted therapy, or biologic agents).   7. Unexpected pregnancy. |
| Study Schedule | Estimated date of the start of the study: August 2019  Estimated enrollment date of the last subject: August 2020  Estimated date of the end of the study: August 2021 |
| Study Procedures | TQB2450 plus anlotinib hydrochloride capsules were administered in a 21-day cycle until disease progression or intolerance. |
| Primary effect endpoints | Duration of response (DoR); overall survival (OS); 12-month progression-free survival rate; disease control rate (DCR); objective response rate (ORR) (assessed per RECIST version 1.1 at the following time points: 3 weeks after the first therapy, then every 6 weeks thereafter during therapy.) |
| Primary safety endpoints | Dose-limiting toxicities (DLT); maximum tolerable dose (MTD); vital signs; laboratory index; adverse event (AE); immune-related adverse event (irAE); serious adverse event (SAE) according to NCI CTCAE version 5.0. |

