**Study Procedures**

| **Visit** | **Screening[1]** | | **Treatment period** | | | | **Post-treatment** | | | **Follow-up of survival** | | |
| --- | --- | --- | --- | --- | --- | --- | --- | --- | --- | --- | --- | --- |
|  |  |  |  |  |  |  | **Withdrawal** | **End-of-**  **treatment** | **Before progression[2]** | | **After progression** | **After DCO[3]** |
|  | 1 | 2 | 3 | 4 | 5+ | 6+[4] | NA | NA | NA | | NA | NA |
| **Visit windows** | -28-0 | -7-0 | ±3 | ±3 | ±3 | ±3 | ±3 | ±3 | ±7 | | ±7 | ±7 |
| **Treatment cycles** | NA | NA | C1D7 | C1D21 | C3D21 | C5D21+ | NA | NA | NA | | NA | NA |
| **Study weeks** | -4-0 | -1-0 | 1 | 3 | 9 | 15+ | NA | With 21 days after treatment discontinuation | Every 6 weeks | | Every 6 weeks | Every 8 weeks |
| **Baseline characteristics** | | | | | | | | | | | | |
| **Informed consent** | X |  |  |  |  |  |  |  |  | |  |  |
| **Demographics** | X |  |  |  |  |  |  |  |  | |  |  |
| **Inclusion/exclusion criteria** | X |  |  |  |  |  |  |  |  | |  |  |
| **Enrollment ID** |  | X |  |  |  |  |  |  |  | |  |  |
| **Physical examination [5]** |  | X | X | X | X | X | X |  |  | |  |  |
| **Vital signs [6]** |  | X | X | X | X | X | X |  |  | |  |  |
| **Medical history [7]** | X |  |  |  |  |  |  |  |  | |  |  |
| **Compliance before enrollment [8]** |  | X |  |  |  |  |  |  |  | |  |  |
| **Radiographic evidence of progression** | X |  |  |  |  |  |  |  |  | |  |  |
| **Laboratory evaluations** | | | | | | | | | | | | |
| **Hemanalysis [9]** |  | X | X | X | X | X | X | X |  | |  |  |
| **Urinalysis [10]** |  | X | X | X | X | X | X | X |  | |  |  |
| **Stool tests [11]** |  | X | X | X | X | X | X |  |  | |  |  |
| **Blood biochemistry [12]** |  | X | X | X | X | X | X | X |  | |  |  |
| **Coagulation function [13]** |  | X | X | X | X | X | X |  |  | |  |  |
| **Thyroid function [14]** |  | X | X | X | X | X | X |  |  | |  |  |
| **Tumor marker** |  | X | X | X | X | X | X |  |  | |  |  |
| **12-ECG [15]** |  | X | X | X | X | X | X |  |  | |  |  |
| **Myo-cardial enzymonram [16]** |  | X |  |  |  |  |  |  |  | |  |  |
| **Echocardiography [17]** |  | X |  |  |  |  | X |  |  | |  |  |
| **Hepatitis B, Hepatitis C, HIV [18]** | X |  | | | | | | | | | | |
| **Pregnancy test [19]** |  | X |  |  |  |  | X |  |  | |  |  |
| **Imaging assessment** | | | | | | | | | | | | |
| **Imaging assessment [20]** |  | X |  | X | At the end of every two cycles (6 weeks ±7 days) | | X |  | X | |  |  |

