12. Blood biochemistry: Liver function (TP, A, G, ALT, AST, LDH, ALP, TBil, DBil, and IBil), renal function (BUN, Cr, and UA), blood lipid tetrachoric (TC, TG, HDL, and LDL), electrolytes (K+, Na+, CL-, Ca2+, Mg2+, and P), lipase, amylase, fasting glucose, etc. are performed within 7 days before enrollment, at C1D7, C1D21, and thereafter at days 21 of every two cycles (odd numbered cycles), and at dropout visit, and at days 21 after treatment; During the drug administration, patients who develop early symptoms of liver injury (e.g., appetite loss, vomiting, right upper abdominal discomfort, malaise, etc.) before blood biochemical abnormalities should undergo blood biochemistry immediately. If ALT or AST is up to 3 times ULN or baseline value and total bilirubin up to 2 times the ULN or baseline value, the frequency of tests should be increased (recommended 1-2 times/week);
13. Coagulation function (PT, APTT, TT, Fbg, and INR) are performed within 7 days before enrollment, at C1D7, C1D21, and thereafter at days 21 of every two cycles (odd numbered cycles), and at dropout visit.
14. Thyroid function (T3, T4, FT3, FT4, and TSH) are performed within 7 days before enrollment, at C1D7, C1D21, and thereafter at days 21 of every two cycles (odd numbered cycles), and at dropout visit.
15. 12-ECG are performed within 7 days before enrollment, at C1D7, C1D21, and thereafter at days 21 of every two cycles (odd numbered cycles), and at dropout visit. If an abnormal ECG is identified, two additional confirmations must be performed (each 5 minutes apart and the QTc interval should be indicated);
16. Myo-cardial enzymonram is detected within 7 days before enrollment. This examination is supplemented only when symptoms such as precordial pain, palpitations, and ECG abnormalities are present;
17. Echocardiography is performed within 7 days before enrollment and at dropout visit. This examination is supplemented only when clinically meaningful ECG abnormalities occur during treatment;
18. Hepatitis B virus (HBV) and hepatitis C virus examination: HBV examination (HBsAg, HBsAb, HBeAg, HBeAb, and HBcAb) is performed and if the test result is abnormal, viral replication (HBA DNA) and hepatitis C virus antibody (anti-HCV) test should be conducted;
19. Pregnancy testing is limited to women of childbearing age, who are required to undergo a pregnancy test within 7 days before enrollment;

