Detection results from other hospitals were also acceptable. Tissue is the first choice for detection samples, if optional blood samples cannot be obtained from tissue, the detection methods can be selected by traditional genetic testing (such as immunohistochemistry, ddPCR, Arms-PCR, etc.) or high-throughput sequencing.

1. At least one measurable lesion according to Response Evaluation Criteria in Solid Tumors (RECIST) version 1.1, without prior radiotherapy in the past three months;
2. Predicted life expectancy of ≥3 months; Eastern Cooperative Oncology Group (ECOG) performance status (PS) of 0-1;
3. Recovered from damages (≤grade 1) associated with other treatments per the CTCAE version 5.0;
4. Adequate function of the important organs as evident by the following criteria:
5. Hemanalysis (no blood transfusion, and without the use of G-CSF or other hematopoietic stimulating factors within 14 days):
6. Hemoglobin (HB) ≥80g/L;
7. Absolute neutrophil count (ANC) ≥1.5×10^9/L;
8. Platelets (PLT) ≥75×10^9/L;
9. Biochemistry:
10. Total bilirubin (TBIL) ≤upper limit of normal value (ULN);
11. ALT and AST ≤1.5×ULN;
12. Creatinine (Cr) ≤1.5×ULN or creatinine clearance rate (CCr) ≥60 mL/min;
13. Urinary protein <++;
14. Coagulation function: INR and APTT ≤1.5×ULN;
15. Doppler ultrasound assessment: left ventricular ejection fraction (LVEF) ≥50%;
16. Women of childbearing potential must have adopted contraception, or have a negative serum and urine pregnancy test within 7 days before the study enrollment; women of childbearing potential and men must agree to contraception for the duration of study treatment and 8 weeks after the last dose of study treatment, or have been of sterilization;
17. Be willing and able to provide written informed consent for the trial, and comply with all aspects of the protocol.
    1. Exclusion criteria

The exclusion criteria were:

1. Patients with a history of malignant tumors within 5 years before the start of treatment except for patients with cured orthotopic cervical cancer, cutaneous basal cell carcinoma, cutaneous squamous cell carcinoma, or superficial bladder cancer (Ta [non-invasive cancer], Tis [orthotopic cancer], T1 [superficially invasive]);
2. Central squamous cell lung cancer or squamous cell lung cancer with a significant pulmonary cavity;
3. Have received >1 systemic chemotherapy during previous lines of treatment (patients with neoadjuvant or adjuvant chemotherapy were allowed to be enrolled);

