19. Hypertension that was uncontrollable with a single antihypertensive drug at present (systolic blood pressure ≥160 mmHg or diastolic blood pressure ≥100 mmHg); or being treated with a combination of two or more antihypertensive drugs;
20. Major surgical operation, biopsy, or obvious traumatic injury within 28 days before enrollment;
21. Virologic testing during screening shows any of the following:
22. HBsAg positive, and HBV DNA ≥1×10^3^ copies/mL;
23. Anti-HCV positive and HCV >ULN;
24. HIV-positive;
25. Immune checkpoint inhibitors or systemic therapies were required to achieve immunosuppression (prednisone or other hormones >10 mg/d);
26. Patients with other anti-cancer therapies or participated in other clinical studies (not EGFR-TKI) within 4 weeks before the first dose of the drug; patients who received therapies or participated in other clinical studies of EGFR TKI within 2 weeks before the first dose of the drug;
27. Imaging showed that the tumor had invaded the important blood vessels, or the tumor was likely to invade the important blood vessels during the subsequent study and cause massive hemorrhage judged by investigators;
28. Patients with any bleeding signs or a history of bleeding, regardless of severity, having grade ≥3 bleeding events per CTCAE, unhealed wounds, anabiosis, or fracture within 4 weeks before grouping;
29. Clinically hemoptysis (daily hemoptysis greater than 50ml) within 2 months before enrollment (defined as coughing up ≥1 teaspoon of blood, small blood clots, or coughing up blood without sputum); but patients with blood in sputum were not excluded;
30. A history of psychotropic substance abuse and cannot be abstinent, or patients with mental disturbance;
31. Have previously received antiangiogenic drugs;

Conditions that increased the risk associated with study participation or the study medication, and could make a patient ineligible for study in the investigator's judgment.

- 1. Screening failure

Failure to establish eligibility within 28 days would result in screening failure and the subject will be excluded from the trial; however, the investigator may decide whether the subjects should undergo appropriate observation or management for re-screening and whether the subjects can be re-entered in the study. In this case, a new ICF will be required to be signed by the subject. Each participant is allowed a maximum of one opportunity for re-screening.

- 1. Withdrawal criteria

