Systematic physical examination, ECOG performance status and vital signs are required to be performed within 7 days before enrollment. Results within±7 days of study completion/withdrawal are allowed at the last visit. Reexamination is required if the examinations are outside the acceptable time window.

All vital signs should be measured in a resting state. If body temperature is measured more than twice in a day, the highest result is recorded.

Blood pressure monitoring: Blood pressure is monitored by the subject himself/herself recorded in the patient diary card. Blood pressure is monitored on alternate days for the first 4 weeks of treatment, at least every 1 week from week 5 to week 12, and at least every 4 weeks thereafter. If blood pressure is abnormal, it should be monitored daily; if blood pressure is normal, normal monitoring frequency can be resumed. Blood pressure is re-measured by investigator at each visit.

- - 1. Laboratory examination

| **Table 6.2-1 6.2.2 Laboratory examination** | |
| --- | --- |
| **Categories** | **Items** |
| Hemanalysis | WBC, ANC, lymphocyte count, red blood cells, Hb, platelet count |
| Urinalysis | red blood cell, white blood cell, and urine protein (analysis of 24-hour urine protein will be performed if necessary) |
| Stool tests | white blood cell, red blood cell, and occult blood |
| Blood biochemistry | ALT, AST, GGT, AKP, TP, ALB, TBIL, DBIL, GLU, BUN/Urea, Cr, UA, K^+^, Na^+^, Cl^-^, Ca^2+^, Mg^2+^, P, LDH, TC, TG, HDL, LDL |
| Coagulation function | INR, APTT, PT, FIB |
| Thyroid function | FT3, FT4, TSH |
| Lipase | Serum lipase (as appropriate) |
| Amylase | Serum amylase (as appropriate) |
| Tumor markers | Serum carcinoembryonic antigen (CEA) |
| Pregnancy | Serum HCG/urineHCG |
| Epidemiology | HbsAg (HBV DNA test for positive HbsAg), HBsAb, HBeAg, HBeAb, HBcAb, Anti-HCV, HIV |

During the screening period, the laboratory tests within 7 days before enrollment are allowed. Results within ±7 days of study completion/withdrawal are allowed at the last visit. Re-examination is required to comply with the requirements of the clinical study if the examinations are outside the acceptable time window.

- - 1. Cardiac function examination

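### A woman already using contraception meets the contraception criterion even with a positive screening pregnancy test, and no exclusion names pregnancy

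*Protocol*

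**What the plan says.** **Entry rule.** The contraception criterion in section 4.2 (printed as item 16) and in the synopsis screening criteria has the same first clause: "Women of childbearing potential must have adopted contraception, or have a negative serum and urine pregnancy test within 7 days before the study enrollment". Its second clause looks forward: "women of childbearing potential and men must agree to contraception for the duration of study treatment", and for 8 weeks after the last dose, with sterilisation as the alternative.

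**Screening test.** Note 19 to the schedule, given under Study Procedures and again in section 6.1, says: "Pregnancy testing is limited to women of childbearing age, who are required to undergo a pregnancy test within 7 days before enrollment". The schedule marks the test at screening visit 2 (day -7 to 0) and at withdrawal. Table 6.2-1 lists the assay as "Serum HCG/urineHCG".

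**Exclusions.** Neither section 4.3 nor the synopsis list names pregnancy or a positive pregnancy test. A different screening test is given binding results: "Virologic testing during screening shows any of the following", followed by the hepatitis B, hepatitis C and HIV findings that keep a patient out. The closing exclusion, which is left to the investigator's judgment, reads "Conditions that increased the risk associated with study participation or the study medication, and could make a patient ineligible for study".

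**Other pregnancy rules.** The synopsis termination criteria include "Unexpected pregnancy". Section 6.5 tells the investigator to stop treatment in a pregnant subject.

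**The concern.** A pregnancy test within a week of enrolment has one purpose at entry: to keep pregnant women from being dosed. The criterion gives the result that force only for women not yet using contraception. For women who already use it, the test is performed but no stated eligibility rule acts on the result.

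What is at stake is fetal exposure to an anti-PD-L1 antibody combined with an antiangiogenic kinase inhibitor, in a multicentre trial where sites screen against the written criteria. The rest of the protocol clearly does not intend pregnant women to be treated, so the entry rule is out of step with the protocol's own later rules. This is a safety point in the eligibility wording, not a statistical one.

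**Working it through.** No figure in the plan needs reproducing. The check is a logical one.

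**Step 1: the first clause as written.** Let C mean contraception already adopted, and N mean a negative serum and urine test in the 7-day window. The clause is met if C or N holds.

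| Contraception adopted | Test | First clause |
| --- | --- | --- |
| Yes | Negative | Met |
| Yes | Positive | **Met** |
| No | Negative | Met |
| No | Positive | Not met |

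A positive test fails the clause only in the last row. The second row is the error.

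**Step 2: does the second clause help?** No. It concerns agreement to future contraception, or sterilisation. It does not mention current pregnancy or the test result.

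**Step 3: does an exclusion help?** No listed exclusion in section 4.3 or the synopsis names pregnancy. The virology item shows how the protocol makes a screening result binding when it wants to. Nothing comparable is written for the pregnancy test, although note 19 requires that test of every woman of childbearing age and exempts no contraception user.

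**Step 4: effect of adding an exclusion for pregnancy or a positive screening test.** Row 2 becomes ineligible. Rows 1 and 3 stay eligible and row 4 stays ineligible.

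**Step 5: effect of also rewording the inclusion clause so that N is required.** The group that loses eligibility is (C or N) without N, that is, C without a qualifying negative result. This is slightly wider than row 2: it also takes in contraception users whose test is missing, out of window, or done on only one of serum and urine. Two points follow.

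- Section 4.2 names serum and urine together, whereas note 19 asks only for a pregnancy test and Table 6.2-1 separates the two assays with a slash. A clause that merely cited the scheduled test could be satisfied by one assay. For women not using contraception that would be looser than the present rule.
- Replacing the alternative by a conjunction (C and N) would exclude row 3, test-negative women who have not yet started contraception but agree to do so. There is no reason to lose them.

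**Step 6: size.** Maximum planned enrolment is 18 (phase I) + 54 (phase II) = 72. The documents give neither the share of women of childbearing potential nor their contraceptive use, so no count can be derived. The case needs a woman of childbearing potential who already uses contraception and tests positive in the 7 days before enrolment.

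**The case against.** The strongest reply is that other rules already keep such a woman from treatment. The closing exclusion covers conditions that raise the risk of the study medication, which pregnancy plainly can. The termination criterion may also reach her before dosing: consent is at visit 1 and the test at visit 2, section 6.5 uses the word subject for someone who has consented but not been dosed (in its definition of pre-treatment events), and the synopsis says a subject must leave the study on "Unexpected pregnancy". Even on a narrower reading she would meet that criterion as soon as she was enrolled, so enrolling her would serve no purpose. The point is then an and/or slip whose intent nobody doubts.

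Much of this stands. A reader might infer that the protocol allows pregnant women to be treated, or that investigator discretion is the only safeguard. The documents support neither inference: the termination criterion can be read as mandatory for her, and section 6.5 directs that treatment be stopped in pregnant subjects. Nor is the test result ignored for everyone, since it decides entry for women not using contraception.

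The reply does not close the gap. The closing exclusion depends on each investigator's judgment. The termination criterion is not an eligibility criterion, and the withdrawal list in section 4.5 does not repeat it. The instruction in section 6.5 presupposes that treatment has started. The withdrawal reason for not meeting the screening criteria does not reach her on this clause, because she meets it. The same wording appears in both places where eligibility is defined, so a slip of drafting or translation would still need correcting.

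**Conclusion.** The criterion is wrong as written for one group: women of childbearing potential who already use contraception and have a positive screening test. They meet it, and no explicit entry rule excludes them. The consequence is minor in scale and probably rare, because the result should be known before dosing and other provisions may well prevent treatment. It is worth correcting because the possible harm is to a fetus and the correction is almost free. No endpoint, sample size, power or analysis is affected. The conclusion rests on the text alone: the plain meaning of the alternative in the clause, and the absence of pregnancy from the exclusion lists in both places. The judgment that the case is rare is an assumption, since the documents give no figure for it.

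**What to change.** Add one line to the exclusion criteria in section 4.3 and in the synopsis: *pregnancy, or a positive pregnancy test at screening*. This alone closes the gap.

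If the inclusion clause is edited as well, it should say that women of childbearing potential must test negative on both serum and urine in the 7 days before enrolment, which keeps the two tests now named. Leave the second clause (agreement to contraception during treatment and for 8 weeks afterwards) unchanged, and do not require that contraception has already been adopted.

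The cost of the exclusion line is one sentence in two places. It adds no visit or procedure, since a test is already scheduled at screening visit 2, and no test-negative woman loses eligibility. The optional rewording could mean one further assay for a contraception user who would otherwise have had only serum or only urine tested.
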